## 7.3. Statistical analysis plan

### 7.3.1. Patient reported outcomes and experiences

#### 7.3.1.1. Summary of baseline data and flow of patients

We will determine the percentage of eligible patients responding at baseline and descriptively compare responders to all eligible patients consulting during the recruitment time period by age, gender, type of musculoskeletal pain, general practice and PCN.

We will report summary statistics (mean and standard deviation, median and interquartile range or frequencies and percentages as appropriate) for each baseline and follow-up measure, overall and stratified by age, gender, and type of musculoskeletal pain. We will also weight responses by age,

gender, and type of musculoskeletal pain distribution of eligible patients to assess the potential impact of non-response on our estimates.

Missing data within responders at each time point should be low but we will use multiple imputation if there are items with >5% missing data.

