### *Baseline patient-reported questionnaire*

**Table 1** lists the patient reported outcome and experience measures to be collected by patient questionnaires. The content of the questionnaire was informed by a cross-mapping of recommended indicator sets [e.g. 28], and measures used in national surveys (e.g. GP Patient Survey, Health Survey for England, FCP evaluation) and previous research studies in the same population and setting. For evaluating social inequalities we used the PROGRESS-Plus framework[29,30] to inform our choice of individual- and area-level social stratifiers.

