## 7 STATISTICS AND DATA ANALYSIS

### 7.1. Sample size calculation

#### 7.1.1. Patient self-reported outcomes (primary objective 2.1.1.)

We anticipate from previous studies and discussions with GP colleagues that the level of practice engagement may wain if the recruitment period extends much beyond 3 months.

The median registered population size of general practices in North Staffordshire & Stoke-on-Trent is 7300. Assuming 80% are aged 18 and over and an annual consultation prevalence for musculoskeletal pain of 15%[33], then there will be 876 patients consulting for musculoskeletal pain on average per practice each year. Across 26 practices (2 per PCN), there will be 5694 eligible patients presenting in the 3-month recruitment period. Assuming a 25% response at baseline and 50% at follow-up, then there will be 1424 baseline responders (1139 (80%) consenting to further contact and record linkages) and 569 responders at 6-month follow-up (**Figure 1**).

**Figure 1.** Estimated number of patients recruited and followed up for the patient-reported outcomes subcohort (NB 3-month period of recruitment per practice).

[figure not shown]

The baseline response of 1424 will allow us to detect a difference of 3 or more points on the MSK-HQ (assuming standard deviation of 10) with 90% power at the 5% significance level for groups defined by a dichotomous covariate with prevalence of 10% (for example ethnicity: black, Asian, and ethnic minority patients vs white).

569 responders at 6-month follow-up will also allow us to detect a difference on the follow-up MSK-HQ of 3 or more points (assuming standard deviation of 10), with 80% power at the 5% significance level, for groups defined by a dichotomous covariate. This is based on a covariate with a prevalence of 10%, 2 follow-up time points (3m and 6m), adjustment for baseline MSK-HQ score, and assumed correlations of 0.5 between the two follow-up scores and between the follow-up and baseline

scores.[34] We will, however, use repeated measures multilevel models to ensure all patients responding at baseline can be included in the analysis.

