#### **7.3.1.2 Primary outcomes analysis**

We will report summary statistics (mean and standard deviation, median and interquartile range) for the MSK-HQ baseline, 3-month and 6-month score and its mean change over 3- months and 6- months overall and stratified by age, gender, and type of musculoskeletal pain. We will also determine the percentage of patients who achieve the minimal important change (MIC) for the MSK-HQ. This has been reported as 6 points, though varies by body region of pain. We will weight responses by age, gender, and type of musculoskeletal pain at baseline.

We will determine patient characteristics associated with baseline MSK-HQ score using multilevel linear regression models (patients nested within practices) including as covariates the key case-mix variables.

To assess inequalities in change in musculoskeletal health over the 6-months, we will use multilevel repeated measures linear regression models (follow-up measures nested within patients) to determine patients characteristics associated with MSK-HQ score at 3m and 6m, adjusting for baseline MSK-HQ score and the case-mix variables.

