#### **7.3.1.4 Sensitivity analysis**

The advantage of using multilevel repeated measures models is that all baseline responders can be included in the analysis even if they do not respond at one or more follow-up points. However, for patients responding at baseline but not at 3 or 6 months, we will also use multiple imputation including baseline and monthly measures (where available) to impute 3- and 6-month follow-up MSK-HQ scores and repeat the analyses above.

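### The imputation trigger in 7.3.1.1 looks at one item at a time, so several items each under 5% missing can together drop a material share of patients from the 7.3.1.2 models without imputation being called for

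*Protocol*

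**What the plan says.** Protocol 7.3.1.1 expects few gaps within returned questionnaires: "Missing data within responders at each time point should be low". It then sets the rule: "we will use multiple imputation if there are items with >5% missing data". It names no handling for items below that limit.

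Protocol 7.3.1.2 fits two multivariable multilevel models. The baseline MSK-HQ model is described as "including as covariates the key case-mix variables". The 3- and 6-month model is described as "adjusting for baseline MSK-HQ score and the case-mix variables". The case-mix variables are neither listed nor counted.

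Protocol 7.3.1.4 adds a sensitivity analysis for patients who answered at baseline but not at 3 or 6 months. Its purpose is "to impute 3- and 6-month follow-up MSK-HQ scores and repeat the analyses above". It does not mention missing covariates.

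Protocol 7.1.1 and 7.3.1.4 both say that the repeated measures models allow everyone who responded at baseline to be analysed.

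**The concern.** A regression loses a patient when any one of its variables is missing. What matters is therefore the share of patients with at least one gap across the model, and the rule never looks at that share. Each item can be comfortably below 5% while the combined share is several times larger.

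Repeated measures models cope with missing outcomes. They do not cope with missing covariates, so they cannot by themselves deliver the inclusion promised in 7.1.1 and 7.3.1.4. When every item is under 5%, nothing in the plan fills the gap.

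At stake is power for primary objective 2.1.1, the gap between disadvantaged and advantaged groups. The follow-up sample is already expected to shrink to 569. If incomplete forms are related to MSK-HQ itself, the estimated gap could be distorted as well.

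**Working it through.** **Inputs from Protocol 7.1.1.** 1424 baseline responders, 569 responders at 6 months, difference 3, SD 10, group prevalence 10%, two-sided 5%, two follow-up points, correlations of 0.5.

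**The plan's own figures.**
- Counts: 7300 × 0.80 × 0.15 = 876 per practice per year; 876 × 26 / 4 = 5694; × 0.25 = 1423.5; × 0.80 = 1138.8; × 0.50 = 569.4. These agree with the protocol.
- Power: SE = SD × √(1/(0.1N) + 1/(0.9N)), power = Φ(3/SE − 1.96).
- Baseline: SD 10, N = 1424, SE = 0.883, power 92.5% (stated 90%).
- Follow-up: variance factor (1 + 0.5)/2 − 0.5² = 0.5, so SD = 10 × √0.5 = 7.07; N = 569, SE = 0.988, power 85.9% (stated 80%).

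The stated powers are slightly conservative, so there is some slack to lose.

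**How much loss uses up the slack.** N needed = ((1.96 + z) × SD / 3)² / 0.09.
- Follow-up, 80%: ((1.96 + 0.842) × 7.07 / 3)² / 0.09 ≈ 485. Tolerable loss 1 − 485/569 ≈ 15%.
- Baseline, 90%: ((1.96 + 1.282) × 10 / 3)² / 0.09 ≈ 1297. Tolerable loss 1 − 1297/1424 ≈ 9%.

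**Loss from several items (assumed counts and rates).** With k items each missing at rate m, the loss is 1 − (1 − m)^k if gaps are independent, and only m if the same patients miss everything. In between, I let the gaps share an equal correlation on a latent normal scale. Table 1 of the protocol has well over a dozen baseline measures, so 6 to 12 covariates is plausible, but the number is not in the plan.

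| Items | Rate | Gaps | Loss | Left of 569 | Follow-up power | Left of 1424 | Baseline power |
|---|---|---|---|---|---|---|---|
| 6 | 3% | correlation 0.7 | 9.6% | 514 | 82% | 1287 | 89.8% |
| 6 | 3% | independent | 16.7% | 474 | 79% | 1186 | 87% |
| 12 | 3% | correlation 0.7 | 13.4% | 493 | 81% | 1233 | 88% |
| 12 | 3% | independent | 30.6% | 395 | 72% | 988 | 81% |
| 12 | 4% | correlation 0.7 | 16.8% | 473 | 79% | 1185 | 87% |
| 12 | 4% | independent | 38.7% | 349 | 66% | 872 | 76% |

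For example, 1 − 0.97^12 = 0.306 and 1 − 0.96^12 = 0.387.

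**Would the rule fire anyway?** It fires once any single item exceeds 5%. For 12 independent items and 1424 responders, the exact binomial chance that at least one observed rate exceeds 5% is under 0.1% at a true rate of 3%, about 29% at 4%, 89% at 4.5% and over 99% at 4.9%. The gap is therefore real at about 3% to 4%, and largely closes just under the limit.

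**The case against.** The protocol never says that complete cases will be used below 5%. It says when imputation will be used, not that it is ruled out otherwise, and the SAP, not shown, may say more. This stands as a limit: complete-case handling is inferred from how regression works by default. The per-item trigger, however, is fixed in the protocol and is the wrong quantity to test.

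The number of covariates and their rates are also assumed. Comorbidity comes from the health record, and age, sex and ethnicity are in the practice extract, so some gaps could be filled. Nothing says that every Table 1 item enters the model. With 6 to 8 items at 3%, independent loss is 17% to 22%. This stands too, and is why the size is given as a range.

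A reader might infer that a dozen items each just under 5% would cost over a third of the sample. The documents do not support that as the expected result. Items truly at 4.9% would almost surely trip the rule, and a loss above a third also needs near-independence; 12 items at 4% with correlation 0.5 lose about 23%.

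A reader might also infer that the group gap must be biased because disadvantaged patients leave more blanks. If missingness depends only on covariates in the model, complete-case coefficients are not biased.

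**Conclusion.** The point holds as a weakness in a stated rule. The trigger tests single items, the models lose patients on any item, and the planned follow-up imputation does not reach covariates. The aim of including all baseline responders is therefore not secured when every item is under 5%, which is the situation that 7.3.1.1 itself anticipates.

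The size is conditional on the number of items, their rates, how far gaps cluster in the same patients, and default complete-case handling. Across 6 to 12 items at 3%, baseline power runs from about 81% to 90%, and follow-up power straddles the stated 80%. At 12 items and 4%, follow-up power is below 80% even with a latent correlation of 0.7. With complete overlap the loss would be only 3% to 4%, and the concern would be minor. Bias in the group gap is possible only if missingness depends on MSK-HQ after conditioning on the model covariates, and the documents give no evidence either way. The change is worth making, but no error in a stated figure has been shown.

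**What to change.** Amend Protocol 7.3.1.1, and the SAP to match, so that multiple imputation is used when more than 5% of participants would be excluded from an analysis model because any of its variables is missing. Alternatively, impute covariates in all models by default, with complete case as a sensitivity analysis. In either form, the imputation model should include the outcome at all time points, the social stratifiers and practice.

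The cost is small. Imputation is already planned in 7.3.1.1 and 7.3.1.4, so the change is a sentence of wording and a little more analysis work. No data collection or sample size changes.

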#### **7.3.1.2 Primary outcomes analysis**

We will report summary statistics (mean and standard deviation, median and interquartile range) for the MSK-HQ baseline, 3-month and 6-month score and its mean change over 3- months and 6- months overall and stratified by age, gender, and type of musculoskeletal pain. We will also determine the percentage of patients who achieve the minimal important change (MIC) for the MSK-HQ. This has been reported as 6 points, though varies by body region of pain. We will weight responses by age, gender, and type of musculoskeletal pain at baseline.

We will determine patient characteristics associated with baseline MSK-HQ score using multilevel linear regression models (patients nested within practices) including as covariates the key case-mix variables.

To assess inequalities in change in musculoskeletal health over the 6-months, we will use multilevel repeated measures linear regression models (follow-up measures nested within patients) to determine patients characteristics associated with MSK-HQ score at 3m and 6m, adjusting for baseline MSK-HQ score and the case-mix variables.

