### 6.2. Strategies to improve inclusion and reduce bias

Participation rates in cohort studies have been declining over several years raising concerns over inefficiency and the potential for selection bias. The use of web-based data collection is increasingly pursued as a low-cost solution to the former problem but may have lower response rates[11] and is still susceptible to selective participation. Internet access in UK households continues to increase year-on-year (96% in 2020[12]) but people most likely to be ‘digitally excluded’ are: older people, people in lower income groups, people without a job, people in social housing, people with disabilities, people with fewer educational qualifications, people living in rural areas, homeless people, people whose first language is not English.[13] These groups may be ‘disadvantaged’ or ‘under-served’[14] and have more complex health needs and poorer outcomes.

The following strategies to improve inclusion and reduce bias are informed by discussions with our Participant Advisory Group, previous synthesis of evidence on the effectiveness of different strategies for survey completion, NIHR INCLUDE[14] and INCLUDE Ethnicity[15] frameworks, previous

experience within the research team, and considerations over what is feasible and affordable for our study.

- Sampling of general practices from across all PCNs in North Staffordshire and Stoke-on-Trent. We will try to over-sample practices in the most deprived neighbourhoods and with a higher proportion of Black, Asian, and minority ethnic patients. To reach a sufficiently diverse population, we will also consider offering study participation to general practices in South Staffordshire and the West Midlands (e.g. Wolverhampton).
- Use of a mixed-mode approach in which those unable or unwilling to complete online questionnaires are offered conventional pen-and-paper self-complete questionnaires.[16] We are not using an explicit 'push-to-web' design (i.e. where web completion is offered as the only mode and alternatives like paper completion are withheld until later on, e.g. for non-respondents).[17]
- The offer of telephone support for questionnaire completion; explicit reassurance that family members can assist (but not substitute) in questionnaire completion for the intended respondent
- The offer of access to a translation service via telephone for study information and questionnaire completion

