- Keeping questionnaire length to a minimum[11,18]; presenting questions in a logical order; minimising cognitive burden of questions; explaining where possible the purpose of questions
- Raising awareness of the survey among the practice and registered patient population prior to going live; using reminders to encourage questionnaire completion[11,18]
- Collection of brief information in the questionnaire on important social characteristics (e.g. date of birth, sex, ethnicity, occupational class, financial strain) to help understand participation, care, and outcomes in under-served groups
- Using pseudoanonymised extracts from the GP clinical system to describe the characteristics of those invited to participate (e.g. Practice Code, Practice Name, Age, Sex, Lower Super Output Area (from postcode), Ethnicity, Method of Invite), as well as the characteristics and patterns of care of the total eligible population of MSK consultants to enable evaluation and possible modelling of selective participation

Those who participate in the study and return either a paper or online questionnaire will be given the opportunity to select a local charity that they would like us to make a donation to. At the end of the initial, 3-month and 6-month questionnaires, participants will be given a choice of four local charities to give to. For every returned baseline, 3-month and 6-month questionnaire £1 will be given to the charity specified by the participant.

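### The stated non-response weights and responder comparison leave out ethnicity, area deprivation and invitation mode, although the protocol plans to extract the data for them on invitees

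*Protocol*

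**What the plan says.** **Weights.** Section 7.3.1.1 weights responses to the age, "gender, and type of musculoskeletal pain distribution of eligible patients to assess the potential impact of non-response on our estimates". Section 7.3.1.2, in its paragraph of summary statistics for the MSK-HQ, says: "We will weight responses by age, gender, and type of musculoskeletal pain at baseline". The regression models follow in separate paragraphs, and no weights are mentioned for them.

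**Responder comparison.** Section 7.3.1.1 compares responders with all eligible patients descriptively on age, gender, pain type, practice and PCN.

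**Data on invitees.** Section 6.2 plans pseudonymised extracts describing those invited ("e.g. Practice Code, Practice Name, Age, Sex, Lower Super Output Area (from postcode), Ethnicity, Method of Invite") and the whole eligible population, "to enable evaluation and possible modelling of selective participation". Section 6.3.1 adds that practices send the study team the invitation method for each patient invited.

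**Expected selection.** Section 6.2 says web-based collection "may have lower response rates[11] and is still susceptible to selective participation". Its list of people most likely to be digitally excluded begins "older people, people in lower income groups, people without a job, people in social housing" and ends with people whose first language is not English. It says such groups may be disadvantaged and "have more complex health needs and poorer outcomes".

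**Objectives.** Objective 2.1.1 concerns differences between disadvantaged and advantaged groups. Objective 2.2.8 is to evaluate non-response and what it implies for bias.

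**The concern.** The protocol names the weighting variables twice, so this is a stated choice and not a detail left open. The choice passes over the variables closest to the study's subject. Weighting on age, gender and pain type corrects selection on deprivation, ethnicity or mode only so far as these track the three variables used.

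What is at stake is the descriptive output (overall MSK-HQ means, MIC percentages) and the answer to objective 2.2.8. If weighted and unweighted figures agree after weighting on three variables, that says little about selection on disadvantage. A reader would nevertheless take the agreement as reassurance.

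**Working it through.** **1. The protocol's own recruitment figures (section 7.1.1).**
- Consulters per practice per year: 7300 × 0.80 × 0.15 = 876.
- Eligible in 3 months over 26 practices: 876 / 4 × 26 = 5694.
- Baseline responders: 5694 × 0.25 = 1423.5, stated as 1424.
- Consenting to contact and linkage: 1423.5 × 0.80 = 1138.8, stated as 1139.
- 6-month responders: 1138.8 × 0.50 = 569.4, stated as 569.

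All four figures reproduce. About 75% of eligible patients give no baseline data, and about 90% (1 − 569/5694) give no 6-month data.

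**2. Variables side by side.**

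| Variable | Planned for invitees (6.2) | Responder comparison (7.3.1.1) | Weights (7.3.1.1, 7.3.1.2) |
|---|---|---|---|
| Age, gender | yes | yes | yes |
| Pain type | not in the example list; named for eligible patients in 7.3.1.1 | yes | yes |
| Practice | yes | yes | no |
| Ethnicity | yes | no | no |
| Deprivation | through LSOA linkage | no | no |
| Invitation mode | yes | no | no |

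**3. Size of error in an overall mean.** The protocol gives no response rates by subgroup, so the rates here are assumptions.
- p: share of eligible patients in the omitted group. The 10% is the prevalence used in section 7.1.1; the 40% is assumed.
- r: the group's response rate relative to everyone else, assumed 0.5 to 0.8.
- D: difference in mean MSK-HQ between the group and the rest, 3 points (the difference targeted in section 7.1.1).
- The group is assumed independent of age, gender and pain type, so the stated weights remove none of the error.

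Share among responders: s = p·r / (p·r + 1 − p). Error in the mean = D × (p − s). Design effect of weighting on this factor: p²/s + (1 − p)²/(1 − s).

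| p | r | s | Error (points) | Design effect |
|---|---|---|---|---|
| 0.10 | 0.80 | 0.082 | 0.06 | 1.004 |
| 0.10 | 0.65 | 0.067 | 0.10 | 1.017 |
| 0.10 | 0.50 | 0.053 | 0.14 | 1.045 |
| 0.40 | 0.80 | 0.348 | 0.16 | 1.012 |
| 0.40 | 0.65 | 0.302 | 0.29 | 1.045 |
| 0.40 | 0.50 | 0.250 | 0.45 | 1.120 |

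Worst case in full: s = 0.20 / (0.20 + 0.60) = 0.25; error = 3 × (0.40 − 0.25) = 0.45; design effect = 0.16/0.25 + 0.36/0.75 = 1.12, so 569 responders carry the information of 569 / 1.12 = 508.

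For an MIC percentage the same formula applies, with D as the difference in percentage points between groups. The error is then about 0.02·D to 0.05·D for the 10% group and 0.05·D to 0.15·D for the 40% group.

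**4. Group contrasts.** If response depends only on the grouping variable, each group's mean is still estimated without bias, and so is the difference. For bias, something further must act differently between groups. Illustration, all assumed: two ethnic groups with 60% and 35% in deprived areas, and a 3-point deprivation effect. The contrast not adjusted for deprivation is then truly 3 × (0.60 − 0.35) = 0.75.
- Deprived patients respond at ratio 0.5 in both groups: shares 0.429 and 0.212, contrast 0.65, error 0.10.
- Ratio 0.5 in the first group and 0.8 in the second: shares 0.429 and 0.301, contrast 0.38, error 0.37.

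A model that includes deprivation as a covariate would deal with this particular mechanism.

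**The case against.** **Effect on the primary contrast.** The strongest objection is that the primary patient-reported objective is a difference between groups, and the weights are stated for summary estimates. A reader might infer that the inequality contrasts stay biased because the weights ignore the exposures. The protocol does not support that: step 4 shows that a group's own response rate does not bias its contrast, and the models adjust for case-mix variables. This objection stands and limits the point to summary estimates and the non-response assessment.

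**Size.** The illustrated errors are small: at most 0.45 points, or 0.045 of the assumed SD of 10, against a 6-point MIC. They also rest on assumed response rates. This stands too.

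**Stated drivers.** A reader might infer that the protocol expects ethnicity and practice to drive non-participation. Section 6.2 is explicit on web mode and on lower-income and other digitally excluded groups. Ethnicity is only implied, through first language and the plan to over-sample practices with more minority ethnic patients, and practice is not named as a driver. The list also starts with older people, and age is weighted. Income and language are not in the example list of invitee variables, so the added variables would serve partly as proxies. Paper questionnaires, telephone support and translation should reduce digital exclusion by design.

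**Provision elsewhere.** Section 6.2 allows for modelling of participation and objective 2.2.8 calls for an evaluation. But modelling is described only as possible, and section 7.3 sets out nothing beyond the three-variable weights and the comparison. The imputation in section 7.3.1.4 concerns baseline responders lost later and does not touch baseline non-response.

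**Precision.** It is tempting to add that a 10% group responding at half the rate would supply only 75 of 1424 responders (5.3%). That is a loss of precision, which weighting cannot restore, so it is no argument for changing the weights.

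**Conclusion.** The point holds for the weighted summary estimates and for objective 2.2.8. The stated weights and responder comparison omit ethnicity, LSOA-derived deprivation and invitation mode, for which the protocol plans the data and, for mode and social disadvantage, itself anticipates selective participation. Under the assumptions shown, the uncorrected error in overall mean MSK-HQ is about 0.06 to 0.14 points for a 10% group and 0.16 to 0.45 points for a 40% group. It would be smaller if the omitted factor tracks age, gender or pain type.

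The main loss is interpretive: the planned check is weak on the kind of selection that matters most to this study. It is not shown that the inequality contrasts are biased; that needs response to depend on a further unadjusted factor or on the outcome, differently between groups. This is a cheap improvement and not a threat to the primary analysis.

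**What to change.** - Add ethnicity (with a category for not recorded), a deprivation measure linked through LSOA, and invitation mode to the response weights in sections 7.3.1.1 and 7.3.1.2, by inverse probability of response or raking.
- Add the same three variables to the responder comparison in section 7.3.1.1, and tie both analyses to objective 2.2.8.
- Report summary estimates weighted and unweighted, and add a weighted version of the inequality models as a sensitivity analysis.
- Invitation mode exists only for patients actually invited, so state whether weights refer to those invited or to all eligible patients, since practices may screen some out.

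Practice in the weights is optional: it is already in the responder comparison and the multilevel baseline model, and there would be only about 55 responders per practice (1424/26). Separate follow-up weights are also optional, since the baseline adjustment and imputation already planned largely cover that ground.

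**Cost.** No new data collection. The weights become somewhat more variable: a design effect of up to about 1.12 for one added factor under the assumptions above, and possibly more with several. Report the effective sample size, and any trimming of weights.

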## **2.2. Secondary objectives**

**2.2.1.** To estimate differences between potentially 'disadvantaged' and 'advantaged' groups of patients in their experiences of primary care MSK consultation [patient-reported outcomes/experiences subcohort]

**2.2.3.** To explore within-practice change in consultation prevalence and recorded management of MSK pain among adults presenting to general practice over time, including comparing current levels with those before COVID (i.e. pre-2020) [EHR-only processes of care]

**2.2.4.** To plot the flow of patients along different MSK care pathways and to define MSK service organisation characteristics for participating general practices and Primary Care Networks (PCNs) [patient-reported outcomes/experiences subcohort]

**2.2.5.** To produce new benchmarked data on processes and outcomes of care for MSK pain conditions at GP practice and PCN levels and to provide new insights into the credibility, validity, and persuasiveness of new visualisations of this MSK health intelligence and present these for feedback from key stakeholders

**2.2.6.** To explore the relationships between identified variations and inequalities in patient care, outcomes, and experiences and their association with wider determinants and organisational characteristics

**2.2.7.** To test case-mix adjustment methods for identifying outliers for recorded processes of care

**2.2.8.** To evaluate patterns of non-response and non-participation and their implications for bias in the above estimates

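### The 3- and 6-month MSK-HQ model names no practice level, although the baseline model does; if outcome and exposure both vary by practice, its standard errors are too small

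*Protocol*

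**What the plan says.** Protocol section 7.3.1.2 states the levels of two models in consecutive paragraphs. Baseline MSK-HQ is analysed with "multilevel linear regression models (patients nested within practices". The 3- and 6-month scores are analysed with "multilevel repeated measures linear regression models (follow-up measures nested within patients", and the adjustment is given as "adjusting for baseline MSK-HQ score and the case-mix variables". The second model names no practice random effect, practice fixed effect or cluster-robust standard error.

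Section 7.3.1.3 repeats these analyses for the minimal important change (by repeated measures logistic models) and for the secondary outcomes, including monthly pain intensity. Section 7.3.1.4 repeats them after multiple imputation. Neither adds a practice term. The practice fixed effect in section 7.3.2.2 belongs to the separate EHR-only models.

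Section 6.2 says that practices will be drawn from all PCNs, with an attempt to over-represent deprived neighbourhoods and practices with more minority ethnic patients. Section 6.3.3 plans social stratifiers at both individual and area level.

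**The concern.** The same patients from the same practices are treated as clustered at baseline and, on the text, as independent at follow-up. The follow-up model serves primary objective 2.1.1, which concerns differences between disadvantaged and advantaged groups over the six months after consultation. Practices are the sampling unit, and the social exposures of interest are expected to differ between them.

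If the adjusted outcome also varies between practices, a model with only scores and patients as levels overstates the information on such exposures. Its confidence intervals are too narrow and its tests reject too often. The same structure would pass to the secondary outcomes and to the imputed-data repeat.

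**Working it through.** **Inputs from protocol section 7.1.1**
- Practices: "Across 26 practices (2 per PCN), there will be 5694 eligible patients presenting in the 3-month recruitment period".
- Follow-up sample and target: "569 responders at 6-month follow-up will also allow us to detect a difference on the follow-up MSK-HQ of 3 or more points", with SD 10, 80% power and a 5% level (taken as two-sided).
- Design: "a covariate with a prevalence of 10%, 2 follow-up time points (3m and 6m), adjustment for baseline MSK-HQ score", with correlations of 0.5 between the two follow-ups and between baseline and follow-up.

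**Assumptions (the protocol gives no ICC)**
- Residual practice ICC of the adjusted outcome, ICC_y: 0.01, 0.02, 0.05.
- ICC of the exposure, ICC_x: 0.1 to 0.3 for a partly clustered patient-level exposure; 0 for one spread evenly; 1 for one fixed by practice.

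**Step 1. The plan's own power figure.** For the mean of two follow-ups adjusted for baseline, SD = 10 × √[(1 + 0.5)/2 − 0.5²] = 10 × √0.5 = 7.07. The groups are 56.9 and 512.1 patients, so SE = 7.07 × √(1/56.9 + 1/512.1) = 0.988. Power = Φ(3/0.988 − 1.96) = 85.9%, against 80% stated. The stated figure is not reproduced, but the difference is on the safe side: about 486 responders would give 80%. The calculation does not mention clustering.

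**Step 2. Responders per practice.** m = 569/26 = 21.9.

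**Step 3. Effect of leaving practice out.** Variance ratio (true over model) = 1 + (m − 1) × ICC_y × ICC_x. SE ratio = √(variance ratio). Actual type I error = 2 × [1 − Φ(1.96/SE ratio)].

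Low end, ICC_y 0.01 and ICC_x 0.1: 1 + 20.9 × 0.001 = 1.021, SE ratio 1.01, type I error 5.2%. High end for a patient-level exposure, ICC_y 0.05 and ICC_x 0.3: 1 + 20.9 × 0.015 = 1.313, SE ratio 1.15, type I error 8.7%.

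| ICC_y | ICC_x = 0 | ICC_x = 0.1 to 0.3: SE ratio | type I error | ICC_x = 1: SE ratio | type I error |
|---|---|---|---|---|---|
| 0.01 | 1.00 | 1.01 to 1.03 | 5.2% to 5.7% | 1.10 | 7.5% |
| 0.02 | 1.00 | 1.02 to 1.06 | 5.5% to 6.5% | 1.19 | 10.0% |
| 0.05 | 1.00 | 1.05 to 1.15 | 6.2% to 8.7% | 1.43 | 17% |

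**Step 4. Check.** The variance of the estimate was computed directly over simulated designs of 26 practices with 22 patients each, for a 10% exposure whose prevalence varies between practices. The SE ratio was 1.01 to 1.03, 1.02 to 1.05 and 1.05 to 1.12 at the three outcome ICCs, with type I error up to 8.4%. A fully practice-level exposure gave 1.10, 1.19 and 1.43. This agrees closely with the formula.

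**Step 5. What it means for an interval.** From step 1 the two-level 95% half-width is 1.96 × 0.988 = 1.94 points. Multiplied by 1.01 to 1.146, the correct half-width of the same estimate would be 1.96 to 2.22 points for a patient-level exposure.

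**Step 6. Power with a practice random intercept.** In the designs of step 4 with exposure ICC 0.1 to 0.3, power for 3 points is about 78% to 84%. The two-level model would claim 82% to 85% in the same designs.

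**The case against.** The bracket may be shorthand. A team that models practice at baseline may intend to keep it at follow-up and name only the level that repeated measures add. The SAP, which is not shown, could settle this. That is possible, and one phrase would then resolve the point. But the protocol does not leave the levels open: it states them for each model, differently, and nothing in it favours the shorthand reading over the literal one.

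The size is also uncertain. Adjustment for baseline score and case-mix may remove much of the practice-level difference, and no exposure ICC is given. This stands. A reader might infer that the standard errors are certainly too small and that the false-positive rate certainly exceeds 5%. The documents support that only if both ICCs are above zero.

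A reader might also apply the practice-level figures to the primary inequality contrasts. The documents do not support this either. Section 7.3.1.2 uses the model for characteristics of patients. Objective 2.2.6, on variations and "their association with wider determinants and organisational characteristics", is secondary and exploratory, and is not assigned to this model. Area stratifiers rest on small areas that patients of one practice need not share. Nor is it certain that practices will differ as intended, since section 6.2 states an attempt to over-sample and not a rule.

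Finally, objective 2.1.1 is about estimation, so interval width is a better yardstick than type I error. Step 5 shows that the change in width is modest for ethnicity.

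**Conclusion.** The inconsistency is in the text, and the literal follow-up model is the weaker of the two. Whether it does harm depends on two quantities that the protocol does not give. Under the assumed ranges, the understatement is small to moderate for a patient-level exposure that clusters in part, such as ethnicity. Area deprivation is likely to be affected more, because it lies closer to practice level, with the fully practice-level case as a ceiling and not the expected effect. An exposure spread evenly over practices is not affected.

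It would be wrong to conclude that the study is underpowered. On the protocol's own inputs its follow-up power statement is conservative, and that margin covers most, though not all, of the scenarios examined for a 10% exposure.

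**What to change.** - In section 7.3.1.2, specify the follow-up linear model as scores within patients within practices, with a practice random intercept and a small-sample correction such as Kenward-Roger for 26 practices.
- Use the same structure for the other linear models in section 7.3.1.3, including monthly pain, and for the imputed-data repeat in section 7.3.1.4.
- For the logistic model of the minimal important change, Kenward-Roger does not carry over. Add a practice random intercept, or use practice-cluster-robust standard errors with a small-sample correction.
- If a practice level was always intended, say so in one phrase.

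The cost is one extra random effect and some wording. No new data are needed and the sample size need not change. Intervals become slightly wider, with the power shown in step 6 of the working.
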